### Participants

The research will be conducted in collaboration with MONAR and AKMED, Polish organizations responsible for overseeing numerous addiction treatment clinics and centers, as well as other independent institutions. Recruitment of participants will target clinical patients who are undergoing either in-patient or out-patient treatment for Substance Use Disorder (SUD). For the in-patient cohort, the study will include individuals who are in the final stage of their therapy, specifically those expected to conclude their treatment within a maximum of 4 weeks but not fewer than 5 days. Eligible participants must be adults, aged 18 years or older, and must possess fluency in Polish. Moreover, in light of the study’s methodology, enrollment will be limited to users of iOS or Android smartphones.

Participants will be recruited into three groups: 1) Patients with alcohol addiction, 2) Patients with cross-addiction (alcohol and stimulants), 3) Patients with cannabis addiction. We plan on recruiting 150 participants with alcohol addiction, 150 participants with cross-addiction, and ~100 participants with cannabis addiction, due to lower availability of CUD therapeutic programs in Poland – and subsequently, less patients finishing therapy.

Each participant will be assigned to either experimental or control condition upon logging in to the mobile app for the first time.

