### Randomization

Upon their initial login to the mobile application, participants in each group (alcohol, cross-addiction, and cannabis), will be randomly allocated to either the experimental or control condition based on a code they receive during recruitment. Codes corresponding to experimental and control conditions were generated seperately for each group and then put in a randomized sequence. The randomization was done via an online randomization tool (45. [Online] Available from: https://www.sealedenvelope.com/simple-randomiser/v1/lists). Block sizes were determined using the simulation tool (45. [Online] Available from: https://www.sealedenvelope.com/randomisation/simulation/, taking into account planned sample sizes. Participants assigned to the experimental condition will gain immediate access to all psychological interventions following their initial app login. Those in the control condition will have access only to the daily EMA questions and the sobriety calendar, a tool for tracking their substance use. They will be provided access to the complete version of the app, including the psychological interventions, subsequent to the study’s conclusion - which is scheduled for 98 days after the first login.

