### Data analysis

Factorial design mixed-effects models will be applied to compare questionnaire battery scores between experimental groups and the control across measurements. In addition, we will perform an interrupted time series analysis to estimate the effects of different types of interventions on longitudinal ecological momentary assessment outcomes.

In the statistical analysis, we will incorporate data from participants who have completed a minimum of 21 Ecological Momentary Assessment (EMA) entries, spread over the one-month period dedicated to evaluating the intervention. For the assessment of the intervention’s enduring effects, the analysis will consider participants who have logged at least three EMA entries during the follow-up phase. In addition, within the intervention group, we will include those who have accessed the app and engaged with the self-guided intervention modules on a minimum of four occasions and at least once, respectively; this will represent the minimal therapeutic exposure required for the study. For the analysis of secondary outcomes, we will include participants who have completed the initial baseline assessment as well as at least one subsequent follow-up assessment.

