Regarding the limitations of the study, we anticipate the potential for a high dropout rate, a common occurrence in previous studies (42) and a concern intrinsic to trials with a longitudinal design. Nonetheless, the inclusion of a contest as an engagement strategy is expected to enhance participant retention rates. It’s crucial to note that the opportunity to win prizes is independent of participants’ self-reported levels of craving or instances of lapses, thereby mitigating any potential bias in their responses.

Drop-out rates in mobile application studies on addiction can be high due to various factors, including lack of motivation, technical issues, limited support and guidance, loss of interest, or intervention design. Lack of adequate support, guidance, or encouragement from researchers or healthcare professionals throughout the study can diminish users’ motivation and commitment to using the application. Reducing dropout rates in mobile applications designed for addiction research requires a combination of strategies to increase engagement and enhance the intervention’s effectiveness. Behavioral tracking and personalized feedback can help users stay motivated and focused on their goals. We will use push notifications and reminders to prompt users to engage with the application regularly, complete tasks, or provide updates. We also provide educational materials and psychological intervention modules based on CBT and mindfulness techniques, which could increase the retention rate and provide support in coping with substance use disorder. We informed users at the beginning of the study that the application could not replace psychotherapy.

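### Participants enter the between-arm analysis according to behaviour after randomisation, with a module-use rule for the intervention arm only, so randomisation no longer protects the comparison

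*Protocol article*

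**What the plan says.** All references are to the protocol article.

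- **Allocation** (Participants): "Each participant will be assigned to either experimental or control condition upon logging in to the mobile app for the first time".
- **EMA rule, both arms** (Data analysis): "we will incorporate data from participants who have completed a minimum of 21 Ecological Momentary Assessment (EMA) entries", counted over the one-month evaluation period.
- **Enduring effects** (Data analysis): "the analysis will consider participants who have logged at least three EMA entries during the follow-up phase".
- **Intervention arm only** (Data analysis): "within the intervention group, we will include those who have accessed the app and engaged with the self-guided intervention modules", with minimums of four app accesses and one module use. The reason given is that "this will represent the minimal therapeutic exposure required for the study".
- **Secondary outcomes** (Data analysis): "participants who have completed the initial baseline assessment as well as at least one subsequent follow-up assessment".
- **Control arm** (Randomization): "Those in the control condition will have access only to the daily EMA questions and the sobriety calendar".
- **Module use** (Mobile application content): the intervention arm may use any module or none, and follows no schedule.

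None of these rules is labelled per-protocol, supplementary or sensitivity. The article describes no other analysis population. It does not say whether the app-access and module-use rule also applies to the secondary outcomes.

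**The concern.** Every rule depends wholly or partly on what a participant does after allocation.

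The module-use rule is the most serious because it has no counterpart in the control arm. A control who would never have opened a module is kept, and the same kind of person in the intervention arm is removed. Because module use is voluntary, the person removed has followed the protocol and received what was allocated.

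The 21-entry rule is the same for both arms, but it can still select differently by arm. The Discussion lists, among its retention measures, "psychological intervention modules based on CBT and mindfulness techniques, which could increase the retention rate", and only the intervention arm has the modules during the study. EMA is also the instrument that records craving and lapses, the primary outcomes. Someone who stops reporting after a lapse may therefore be removed for a reason linked to the outcome.

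The stated aim is effectiveness. Under these rules the estimate describes intervention participants who reported and used a module against controls who reported, and a difference between those groups need not be caused by the app. The article expects only small effects, so a modest bias matters.

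**Working it through.** **1. The plan's own figure.** The Sample size calculation section gives 360 participants for 80% power, from a simulated mixed model with a small effect. It states no numerical effect, alpha, intraclass correlation or number of measures, so 360 cannot be uniquely reproduced. With one measure per person, two-sided 5% and 1:1 allocation, 80% power needs 786 in total at 0.2 SD and 360 at 0.296 SD. The figure is neither confirmed nor contradicted, and the point does not rest on it.

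**2. Which rule separates the arms.** Someone with 21 EMA entries has almost certainly opened the app four times. Once the common EMA rule is applied, what remains specific to the intervention arm is one use of a module.

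**3. Inputs for the illustration.** Planned recruitment is 150 + 150 + about 100 = about 400 (Participants), taken as 200 per arm. All other inputs are assumptions, because the documents give no pass rates or correlations:
- no true effect;
- EMA adherence A and propensity to use modules M are standard normal with correlation 0.5;
- the outcome (higher = better, SD 1) has correlation r with each of A and M;
- 70% meet the EMA rule in both arms, so any differential selection by that rule is left out;
- a share k of all intervention participants would meet the module rule.

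**4. Formulas.** The regression of the outcome on A and M has coefficient r/(1 + 0.5) = r/1.5 on each.
- Control mean after the EMA rule: r × φ(a)/0.7, where a is the 30th percentile of the standard normal. This is 0.497r.
- Intervention mean after both rules: (r/1.5) × (E[A | both rules met] + E[M | both rules met]).
- Bias = intervention mean minus control mean.

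For k = 80%, the two conditional means are 0.548 and 0.461. Then 1.008/1.5 − 0.497 = 0.175, so the bias is 0.175r. For k = 60%, they are 0.616 and 0.707. Then 1.323/1.5 − 0.497 = 0.386 (from unrounded values), so the bias is 0.386r.

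Controls analysed: 200 × 0.7 = 140. Intervention participants analysed: about 123 (k = 80%) or 98 (k = 60%). The SE is √(1/140 + 1/123) = 0.124 or √(1/140 + 1/98) = 0.132. With b = bias/SE, the two-sided rejection rate is 1 − Φ(1.96 − b) + Φ(−1.96 − b).

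**5. Results with no true effect.**

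| r | k | Bias (SD) | Type I error |
|---|---|---|---|
| 0.2 | 80% | 0.035 | about 6% |
| 0.2 | 60% | 0.077 | about 9% |
| 0.3 | 80% | 0.053 | about 7% |
| 0.3 | 60% | 0.116 | 14% to 15% |
| 0.3 | 90% | 0.024 | about 5.5% |
| 0 | any | 0 | 5% |

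The range in the fourth row depends on whether the SE uses an SD of 1 or the slightly smaller SD after selection. A negative r reverses the sign: with r = −0.2 and k = 70% the bias is −0.055 SD.

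**6. Numbers lost.** Under these assumptions, 140 + 123 = 263 or 140 + 98 = 238 participants are analysed, below the stated minimum of 360. Keeping 360 of about 400 would need 360/400 = 90% to pass the filters.

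**The case against.** Several points on the other side carry weight.

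- **Size.** A reader might apply the intervention-only filter to a whole unselected arm. With 180 per arm, that gives 0.15 SD and about 25% type I error (70% passing, r = 0.3), or 0.19 SD and about 36% (60% passing, r = 0.3). The documents do not support that model. The 21-entry rule applies first and to both arms, it already removes the least engaged controls, and one module use is a low bar for those left.
- **Direction.** A reader might infer that the rule must favour the app. That requires module users to have better outcomes anyway. The Introduction presents such apps as help during heightened craving, and use is at the participant's discretion, so those who open modules may be those doing worse. The documents do not decide this.
- **Retention.** The Discussion says only that the modules, listed with educational materials and reminders, could raise retention. That makes differential selection by the EMA rule possible. It does not make it an expectation of the plan.
- **Legitimate use.** The single-session hypothesis and the interrupted time series by type of intervention concern module users and need such a restriction.
- **Other documents.** The pre-registration and any SAP are not shown. The most that can be said is that this article states no all-randomised analysis.

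All of these stand, and they limit the size and certainty of the claim. None of them justifies a one-arm exposure rule in the between-arm comparison. That rule is stated in the text, so it is not a detail left to another document.

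**Conclusion.** The point holds. As written, the comparison of craving and lapses depends on behaviour after allocation, and one condition can be met or failed in the intervention arm only. Randomisation therefore does not protect it.

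The bias could go either way. Under the stated assumptions, the module-use rule alone gives about 0.03 to 0.12 SD and a type I error of about 6% to 15%. This shows scale and does not estimate the bias in this trial. The bias is negligible if nearly all EMA-adherent intervention participants use a module, or if engagement is unrelated to outcome, and the documents give no figure for either. Differential selection by the 21-entry rule would come on top and is not quantified.

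The rule requiring baseline plus one follow-up for secondary outcomes applies to both arms and is much milder. It is not part of the main criticism.

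**What to change.** Before outcomes are analysed:

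1. Define the primary between-arm analysis of craving and lapses as all participants allocated at first login, in their allocated arm. Use all available EMA entries in a likelihood-based mixed model, with no minimum-entry or module-use rule. Such a model can use partial series.
2. Keep the 21-entry, three-entry and app-access/module-use rules for analyses labelled per-protocol or sensitivity.
3. Keep the module-use restriction for the single-session and interrupted time series analyses, and say that they concern module users.
4. State whether the app-access and module-use rule was meant to apply to the secondary outcomes. If so, remove it from that between-arm comparison too.

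The cost is a change of wording in the plan and registration and slightly more analysis, with no new data collection. The estimated effect may be smaller because non-users are included.

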### Data management

Throughout the duration of the research, longitudinal data will be systematically collected via the Nałogometr 2.0 app and securely stored on a protected server. Documentation of this data will comprise codebooks outlining essential information, including data collection protocols, methodological approach, and participant sample characteristics. These codebooks will also detail the types of measures that correspond to each unit of raw data.

The roles of data stewards will be assigned to the Principal Investigators (PIs) and Co-Investigators (CIs), who will oversee the documentation and management of data throughout the processes of collection, analysis, and the eventual dissemination of findings. Team members such as project coordinators, data scientists, and analysts will access the data solely in an anonymized format, adhering to the directives set forth by the PIs and CIs.

After the results have been published, the data will be archived on a server with comparable security measures. Depending on the research phase and the questions being explored, data will be queried and extracted as ASCII files. This anonymized data, including individual participant identifiers, demographic details, and pertinent variable labels and values, will then be made accessible to additional project staff. Subsequently, these team members will undertake any data transformations required to prepare the data for publication-oriented analyses.

Each additional staff member will be obligated to produce documentation describing what data was used and how was it transformed for completing the research task they were involved in. This will include documentation pertaining to the decisions related to any data transformations and coding performed, including variable lists and definitions of the raw data used and how the derived variables were created. Analytical methods and techniques performed for any particular research task will also be documented.

Publications derived from the data collected in this study will strictly utilize anonymized (de-identified) datasets and will focus on presenting results at an aggregate level. Given the anticipated absece of (high) risk to participants, the formation of a data monitoring committee has been deemed unnecessary for this study.

Every additional staff member involved in the research will be required to generate thorough documentation detailing their use and transformation of data in the execution of their assigned research tasks. This documentation will include an explanation of the decisions that guided data transformations and coding, inclusive of comprehensive lists and definitions of the variables derived from raw data, as well as descriptions of the analytical methods and techniques applied in each specific research task. This documentation process ensures transparency and reproducibility of the research findings, and it assists in maintaining the integrity of the data analysis process.

## Discussion

In this protocol, we detail the framework for a two-arm randomized controlled trial aimed at evaluating the efficacy of CBT and mindfulness-based mobile intervention modules administered through the Nałogometr 2.0 app. The objective is to ascertain the impact of these mobile interventions in mitigating cravings and lapses associated with SUD. By examining the utility of the interventions across clinical populations with distinct addiction profiles—alcohol, cannabis, and mixed (alcohol and stimulants) addiction—we aim to gauge the effectiveness of the intervention modules for various manifestations of SUD.

Patients with SUD face a high risk of relapse post-treatment, with estimates suggesting that 40-80% of individuals relapse into addiction following the conclusion of therapy. Mobile psychological intervention modules stand as a potentially powerful means of supporting patient recovery and enhancing the long-term outcomes of treatment. Should the interventions prove effective, they could make a significant contribution to the domain of addiction therapy, representing a valuable asset in the ongoing effort to prevent lapses and relapses.

Furthermore, the study will encompass exploratory analyses aimed at discerning whether the efficacy of the interventions correlates with user engagement levels within the app and subsequent alterations in other psychological domains, such as impulsivity, sensation seeking, stress management, and emotion regulation. These analyses will also consider physical functioning indicators collected through physiological metrics, including heart rate, sleep quality, and activity levels. Delving into this ancillary data will provide deeper insights into the recovery mechanisms from SUD and could inform the enhancement of future health interventions for addictive disorders.

The proposed randomized controlled trial (RCT) will focus on a post-therapy clinical patient population—a demographic that is particularly susceptible to relapse. Conducting the study within the naturalistic settings of the patients ensures the ecological validity of the results and the derived conclusions. Through the collection and analysis of longitudinal data over a span of three months, complemented by regular monthly follow-up assessments, the research aims to elucidate the dynamics of post-therapeutic shifts in cravings and behaviors in patients with SUD.

Regarding the limitations of the study, we anticipate the potential for a high dropout rate, a common occurrence in previous studies (42) and a concern intrinsic to trials with a longitudinal design. Nonetheless, the inclusion of a contest as an engagement strategy is expected to enhance participant retention rates. It’s crucial to note that the opportunity to win prizes is independent of participants’ self-reported levels of craving or instances of lapses, thereby mitigating any potential bias in their responses.

Drop-out rates in mobile application studies on addiction can be high due to various factors, including lack of motivation, technical issues, limited support and guidance, loss of interest, or intervention design. Lack of adequate support, guidance, or encouragement from researchers or healthcare professionals throughout the study can diminish users’ motivation and commitment to using the application. Reducing dropout rates in mobile applications designed for addiction research requires a combination of strategies to increase engagement and enhance the intervention’s effectiveness. Behavioral tracking and personalized feedback can help users stay motivated and focused on their goals. We will use push notifications and reminders to prompt users to engage with the application regularly, complete tasks, or provide updates. We also provide educational materials and psychological intervention modules based on CBT and mindfulness techniques, which could increase the retention rate and provide support in coping with substance use disorder. We informed users at the beginning of the study that the application could not replace psychotherapy.

Drawing from existing literature on mobile interventions for substance use reduction, we are prepared for the possibility of observing only small effect sizes (25). The clinical relevance of a therapeutic intervention is contingent upon externally established standards by researchers and other healthcare professionals. There needs to be more consensus concerning the precise criteria for delineating these efficacy standards. Such criteria may encompass a diminished proportion of treated subjects experiencing adverse outcomes or being susceptible to them, resolution of the targeted issue, or achievement of normative levels of functioning post-intervention. Jacobson et al. (59) delineated clinical significance as a transition towards normal functioning attributable to therapy and outlined methodologies for identifying patients manifesting statistically reliable changes considered clinically significant as per their delineation. Providing a definitive recommendation for a specific effect size that clinicians could universally employ to infer clinical significance poses considerable challenges (60). Despite this, any indication of the mobile interventions’ effectiveness could still be of significant clinical relevance, contributing valuable knowledge to the field of SUD treatment.

## Ethics statement

The study procedures contributing to this work comply with the ethical standards of the Declaration of Helsinki. Ethical approval has been obtained from the Institute of Psychology Polish Academy of Science Ethics Committee (26/XII/2022). The protocol has been registered at a clinical trials database (NCT05730504).
